Concerns remain regarding the level of iron in therapeutic or supplementary food despite some studies showing the positive effect of iron supplementation on growth [42]. These concerns are related to the potential side effects that some studies have attributed to iron fortified food of inducing an increase in the population of pathogenic bacteria in the gut[43, 44]. In the case of RUTF, and especially of SMS-RUTF that may have higher level of phytates than P-RUTF, an increase in iron content was justified by the fact that an unpublished study conducted in Senegal showed that treatment with P-RUTF was not associated with a significant increase in haemoglobin (HB) while treatment with the therapeutic milk (F100) fortified with iron to provide 3mg/kg/day was associated with a significant increase in haemoglobin [45]. In the F100 group, HB increased from 83.1 g/L (95% CI: 77.0-89.1) to 91.4 g/L (95% CI: 86.1-96.7) during rehabilitation ( $P < 0.001$ ). In the RUTF group, HB increased from 85.4 g/L (95% CI: 80.4-90.3) to 87.1 g/L (95% CI: 80.9-93.2)[45]. The associated iron deficiency anaemia among children with SAM was confirmed in another recent study conducted in Turkey[46]. Also, a recent study in Malawi has suggested that iron can be safely prescribed to children recovering from severe malaria, a condition that in the past has been associated with very high post-discharge mortality [47, 48].

Despite several studies that have shown that nutrition therapy with appropriate diet is associated with increase in free fat lean mass including muscle volume increase, there has been a continued debate around the possible association between rapid weight catch up growth observed during nutrition rehabilitation of SAM, higher amounts of body fat deposition and insufficient repletion of muscle and visceral proteins – all occurring without full corrections of vitamins and mineral deficiencies[49-52]. Data from the recently completed SMS-RUTF

study in DRC has shown that the fear of excess fat deposition is not justified when RUTF is used as there was no excess fat deposition either with SMS-RUTF or with P-RUTF when compared to community controls. In addition, the Bio-electrical impedance (BIA) parameters collected during this study were still improving at the time of discharge, suggesting that the recovery of the electrical tissues properties was not complete.

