Although the information available on the cost-effectiveness of therapeutic feeding centres, and especially community-based management approaches, is sufficient to justify the inclusion of the management of SAM in the child survival strategy, there is still resistance from some policy makers and donors to invest in this intervention over the long term [10, 18, 70-74]. A commonly cited reason behind this resistance is the supposed persistence of a high risk of mortality after recovery from SAM once the patient has exited a treatment programme [75-78]. Data on the longer term mortality associated with discharge from inpatient therapeutic feeding centres is variable; some studies have reported a cumulative mortality rate after 1 to 1.5 years from discharge of up to 41% [75, 76, 79-82], whilst others have reported lower figures of 2.3% after 12 months of follow up, and 4.1% after 1.5 years of follow up [11, 83]. An earlier study reported a mortality of 1.5%, 12 months after discharge among children treated using the domiciliary approach [83]. None of these studies assess the reasons behind the high mortality after discharge from therapeutic feeding programmes, nor do they examine how post-discharge mortality compares with the mortality rate of all children in the same community. Given the strong association between high childhood mortality, poverty and SAM, it may be that baseline mortality rates partly explain both the observed high post discharge mortality and the study- to-study variation. One study that reviewed the existing evidence on long term mortality has shown that children treated in CMAM programmes who start nutrition rehabilitation at an early stage of metabolic malnutrition have long term survival that is comparable to that of children in the same community [84].

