#### Other secondary hypotheses:

- 6 Haemoglobin gain of children treated for SAM with FSMS-RUTF will not be lower than that of children treated with MSMS-RUTF nor than that of those treated with P-RUTF given a margin of non-inferiority of 0.5g/dl.
- 7 The RUTF daily intake in grams and in kcal/kg/day of children 6 to 59 months old treated for SAM with FSMS-RUTF will not be inferior to the daily intake of children of the same age treated with MSMS-RUTF nor to the daily intake of those treated with P-RUTF given a margin of non-inferiority of 18g/day and 25kcal/kg/day, respectively (age group 6 to 23 months and 24 to 59 months to be sampled and analysed separately).
- 8 Breast milk intake of children 6 to 23 months old treated for SAM with FSMS-RUTF will not be lower than the breast milk intake of children of the same age treated with MSMS-RUTF nor to the intake of those treated with P-RUTF given a margin of non-inferiority of 100g/day.
- 9 Proportion of children with normalised stool calprotectin at 14 days, 28 days and recovery will not be lower in children treated for SAM with FSMS-RUTF than in those treated with MSMS-RUTF or in those treated with P-RUTF given a margin of non-inferiority determined using the synthesis method based on the confidence interval observed in children treated with P-RUTF.
- 10 Plasmatic level of key growth related AA of children treated with FSMS-RUTF will not be inferior to that of children treated with MSMS-RUTF or P-RUTF given a margin of non-inferiority defined using the synthesis method
- 11 12-months after discharge survival in children with SAM treated with FSMS-RUTF will not be inferior to that of children treated with MSMS-RUTF nor to that of those treated with P-RUTF given a margin of non-inferiority of 10%.

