### 2.3.3 Margin of non-inferiority

The margin of non-inferiority was fixed using the margin fixed method except for the secondary specific objectives 8, 15 and 16 of the efficacy trial, for which the synthesis method will be used. The margin for the recovery rate of 10% and of the time to recovery of 14 days were used in our previous study and was accepted by the reviewers of journals that have published the findings [15, 92]. All the other non-inferiority margin stated are based on the 95% confidence interval of the difference observed in our recent SMS-RUTF efficacy trial conducted in DRC (paper in preparation).

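### The 10-point margin for 12-month post-discharge survival is 4.3 to 6.7 times the two 12-month mortality figures that the protocol cites, so a doubling of such mortality would very probably, and a tripling quite possibly, be called non-inferior

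*Protocol*

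**What the plan says.** **Survival.** Hypothesis 11, under Other secondary hypotheses in Protocol sections 1.2 and 2.3.2.2, compares 12-month post-discharge survival on FSMS-RUTF with MSMS-RUTF, "nor to that of those treated with P-RUTF given a margin of non-inferiority of 10" per cent. The scale is not stated. Section 2.5.1.2 lists deaths after discharge among the principal endpoints and expresses them per person-time. Section 2.5.6.2.1 plans Kaplan-Meier curves, a log-rank test and a Cox model, but describes them for recovered children against community controls, not for arm against arm. Table 2 has no survival row.

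**Mortality cited in section 2.1.** On inpatient centres: "some studies have reported a cumulative mortality rate after 1 to 1.5 years from discharge of up to 41" per cent, "whilst others have reported lower figures of 2.3% after 12 months of follow up, and 4.1% after 1.5 years of follow up". On the domiciliary approach: "An earlier study reported a mortality of 1.5%, 12 months after discharge among children treated using the domiciliary approach".

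**Haemoglobin.** Hypothesis 6 compares haemoglobin gain "given a margin of non-inferiority of 0.5g/dl". For the RUTF group of an unpublished study, section 2.1 reports: "HB increased from 85.4 g/L (95% CI: 80.4-90.3) to 87.1 g/L (95% CI: 80.9-93.2" g/L). It describes this change as not significant.

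**Source of the margins.** Section 2.3.3 justifies the margins for recovery rate and time to recovery by earlier use, assigns a few objectives to the synthesis method, and then says: "All the other non-inferiority margin stated are based on the 95% confidence interval of the difference observed in our recent SMS-RUTF efficacy trial". Those figures are not shown. Hypotheses 6 and 11 carry fixed numbers, so I read both as falling under this sentence.

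**The concern.** A non-inferiority margin for mortality should be small relative to the mortality expected on the standard food. Otherwise the test cannot separate an acceptable food from one that several times as many children fail to survive. Here the margin exceeds the whole expected event rate at the two 12-month figures cited. A true difference at the margin would be 12.3% against 2.3%, or 11.5% against 1.5%.

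The stated source does not remove the worry. An interval for the earlier SMS-RUTF against P-RUTF shows how much worse the predecessor might have been. It does not show how much of the benefit of P-RUTF has to be kept.

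Section 2.2 says that efficacy should not rest on anthropometry alone and names long-term mortality as an important endpoint. A survival non-inferiority statement would therefore be read as reassurance about safety.

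**Working it through.** **1. The plan's own figure.** There is no survival sample size to reproduce. The only row tied to either margin is SO11 (haemoglobin): SD 1.3, margin 0.5, 80% power. With one-sided 5%, n = (1.645 + 0.842)² × 2 × 1.3² / 0.5² = 83.6, so 84, and 84/0.9 = 94 after 10% loss. Table 2 gives 100, which looks like rounding up and is not a material discrepancy.

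**2. Margin against cited mortality.**
- 12 months: 10/2.3 = 4.3 and 10/1.5 = 6.7.
- 1.5 years: 10/4.1 = 2.4.
- Highest figure: 10/41 = 0.24.

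**3. Children per arm (assumption).** Table 2 enrolment less 10% loss, times the recovery assumed there:
- 6 to 23 months: 250 × 0.9 × 0.755 = 170.
- 24 to 59 months: 150 × 0.9 × 0.882 = 119.
- Pooled: 289.

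Hypothesis 11 is silent on age. Section 1.5.4.2 says that the age groups are analysed separately except for body composition and haemoglobin, so both readings are shown.

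**4. Probability of being declared non-inferior.** The rule is: observed difference in deaths + z × SE < 0.10, with SE² = p₁(1−p₁)/n + p₀(1−p₀)/n. All binomial outcomes were enumerated. In each cell the lower value uses the two-sided 95% interval (figure legend in section 2.5.6.2.1) and the higher the one-sided 95% limit (section 1.5.3.2).

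| Control mortality | True ratio | 289 per arm | 170 per arm | 119 per arm |
|---|---|---|---|---|
| 1.5% | 2 | >0.99 | >0.99 | 0.97–0.99 |
| 1.5% | 3 | 0.995–0.998 | 0.94–0.97 | 0.84–0.91 |
| 2.3% | 2 | 0.997–0.999 | 0.95–0.98 | 0.87–0.93 |
| 2.3% | 3 | 0.86–0.91 | 0.66–0.76 | 0.53–0.64 |
| 4.1% | 2 | 0.83–0.90 | 0.63–0.73 | 0.50–0.60 |
| 4.1% | 3 | 0.13–0.21 | 0.10–0.17 | 0.09–0.15 |

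Example: 7 deaths of 289 (2.4%) on P-RUTF against 26 of 289 (9.0%). The difference is 6.6 points, SE 1.9, and the one-sided upper limit 6.57 + 1.645 × 1.91 = 9.7, which is below 10. The food passes.

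**5. Ease of passing.** With equal mortality of 2.3%, n = 6.18 × 2 × 0.023 × 0.977 / 0.10² = 28 per arm gives 80% power.

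**6. Haemoglobin.** The cited gain is 87.1 − 85.4 = 1.7 g/L = 0.17 g/dl, and 0.5/0.17 = 2.9. With 90 evaluable per arm (100 less 10%), SE = 1.3 × √(2/90) = 0.194. The largest passing observed deficit is 0.5 − 1.645 × 0.194 = 0.18 one-sided, or 0.5 − 1.96 × 0.194 = 0.12 two-sided. A food with zero gain (true deficit 0.17) passes with probability Φ((0.18 − 0.17)/0.194) = 0.52 or Φ((0.12 − 0.17)/0.194) = 0.40.

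**The case against.** **The mortality figures vary.** Section 2.1 calls the inpatient data variable and puts 41% and 2.3% in one sentence. If control mortality were near the top of that range, 10 points would not be excessive, and at 4.1% a tripling would usually fail. This limits the claim to low mortality. Low figures are nevertheless the natural planning range for a community day-care trial: the 1.5% is for domiciliary care, and section 2.1 reports that children treated early in CMAM programmes survive about as well as others in their community.

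**A margin is not a pass mark.** A reader might infer that the plan accepts 12% mortality. It does not. A true difference at the margin passes only about 5% of the time or less. What passes readily is a doubling and, less surely, a tripling.

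**The reading rule gives some protection.** The figure legend in section 2.5.6.2.1 treats an interval inside the margin that excludes zero as non-inferior and also inferior. The chance of excluding zero is about Φ(d/SE − 1.96). For a tripling from 2.3% with 289 per arm, 0.046/0.0173 − 1.96 = 0.70, so about 0.76. For a doubling, 0.023/0.0152 − 1.96 = −0.44, so about 0.33, and less by age group. The rule catches only part of these cases.

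**Haemoglobin.** A reader might infer that this test, too, would pass a clearly worse food. At the planned size it only could: about 40 to 52% for a zero-gain food, measured against one unpublished, non-significant change with wide intervals. If about 321 per arm were measured (250 × 0.755 + 150 × 0.882, an assumption), the figures would be 0.90 to 0.94.

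**The source in section 2.3.3.** A reader might infer that the earlier trial's intervals should be struck out as a basis altogether. That sentence also supports the margins for weight gain, height, fat mass, intake and breast milk, which would then have no source. The figures behind it are not shown, so they cannot be judged here.

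**Conclusion.** The point holds for survival. At the 12-month mortality of 1.5% or 2.3% that the Protocol cites, a doubling on FSMS-RUTF would be declared non-inferior with probability 0.87 or more under every reading. A tripling would pass with probability 0.86 to above 0.99 pooled and 0.53 to 0.97 by age group. At 4.1% the problem is smaller, though a doubling still passes with probability 0.50 to 0.90.

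This rests on four assumptions: the margin is in percentage points; about 289 recovered children per arm are followed (170 and 119 by age group); the test is a simple interval for the risk difference; and control mortality is in the low range cited.

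The haemoglobin margin is a minor note: a zero-gain food could pass, but that is not assured.

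A reader might infer that the trial's main result is compromised. It is not. Both are other secondary hypotheses, the sample size rests on the primary objectives, and the recovery-rate conclusion is untouched. This should be fixed, but it is not a condition for going ahead.

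**What to change.** **Hypothesis 11 (sections 1.2 and 2.3.2.2).** Delete the 10% margin and the non-inferiority wording. State instead that 12-month post-discharge mortality will be compared between arms by the risk difference and the hazard ratio, each with a 95% confidence interval, without a non-inferiority claim. In section 2.5.6.2.1, add the between-arm comparison to the Kaplan-Meier and Cox methods already planned against community controls.

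**Do not substitute a tighter margin chosen to fit the available numbers.** A 3.5-point margin, for example, has 80% power with 289 per arm at 2.3% mortality (two-sided 95% interval: 3.5/1.247 − 1.96 = 0.85). Its power is only 58% with 170 per arm and 44% with 119, and 56% pooled at 4.1%. It has no clinical basis either.

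**Hypothesis 6.** Report the between-arm difference in haemoglobin gain with its confidence interval as the main result.

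**Section 2.3.3.** Leave the other margins as they are.

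**Cost.** Wording only, with no extra children or measurements. The small loss is an easy non-inferiority statement on a secondary endpoint.

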### 2.3.3 Margin of non-inferiority

The margin of non-inferiority was fixed using the margin fixed method except for the secondary specific objectives 8, 15 and 16 of the efficacy trial, for which the synthesis method will be used. The margin for the recovery rate of 10% and of the time to recovery of 14 days were used in our previous study and was accepted by the reviewers of journals that have published the findings [15, 92]. All the other non-inferiority margin stated are based on the 95% confidence interval of the difference observed in our recent SMS-RUTF efficacy trial conducted in DRC (paper in preparation).

## 2.4 Setting

The research programme will be conducted in the Central Region of Malawi. For the acceptability trial, two CBCCs will be used for the study. We have pre-agreement with several CBCCs but the final choice of the CBCCs will be made in January 2015 based on the functionality and on the number of children attending the centres at that time. The efficacy trial will be carried out in 3 Health District of the Central Region as recommended by the Ministry of Health. These Health Districts are Lilongwe, Dedza and Mchinji. Pre-agreement have been secure with the District Health Officers (DHO) of these Health Districts. In each Health District, a Cluster (a sub-administrative area in Malawi administrative organisation) with the highest burden of acute malnutrition according to the 2014 monthly routine statistics will be selected. In total, 30 community based feeding centres will be established (10 in each District) in the catchment areas of OTP sites that reported more than 60 admissions of SAM cases in 2013. The list will be finalised based on the 2014 statistics and after a field visit has cross-checked the routine statistic figures. The Central region has the worst indicators for undernutrition among under-five children. During the 2010 Malawi Demographic Survey, the prevalence of stunting was 47.2% while that of underweight was 13.5%. The prevalence of wasting is low at 1.8% for severe wasting and 4.3% for wasting. However, this figure underestimates the actual incidence of SAM because up to 80% of cases are oedematous in Malawi and they are not included in these statistics[93]. Indeed, according to

Ministry of Health, by the end of August 25,313 children with SAM had been admitted to CMAM in 2013/2014 consumption year (UNICEF, Malawi situation report, July and August 2014).

## 2.5 Methods

### 2.5.1 Study design

#### 2.5.1.1 Acceptability trial

This will be a cross-over trial. In each site, children will be divided in 2 groups. In 2 separate phases, each group will alternatively receive one of the study food (FSMS-RUTF or MSMS-RUTF) and the control food (P-RUTF). The sequences of the phase will be as indicated in the table 1 below:

**Table 1: Cross-over sequences.**

| SITE     | ARM          | PHASE 1   | PHASE 2   |
|----------|--------------|-----------|-----------|
| NUMBER 1 | INTERVENTION | FMSM-RUTF | P-RUTF    |
|          | CONTROL      | P-RUTF    | FMSM-RUTF |
| NUMBER 2 | INTERVENTION | MSMS-RUTF | P-RUTF    |
|          | CONTROL      | P-RUTF    | MSMS-RUTF |

As indicated above, the principal endpoints of the acceptability trial are:

1. Acceptability defined by the criteria listed below
  - a. Persistence of good appetite
  - b. Consumption of more than 75% of the offered food within 1 hour. (meal acceptance)
  - c. Consumption of more than 75% of the offered food for more than 75% of the days on trial (overall acceptance)
  - d. Consumption of a quantity of energy not less than 75% of the energy intake from the control food.
2. Tolerance that is confirmed if:
  - a. ill-effects associated with the food requiring withdrawal from the trial is less than 10% and if the
  - b. The difference in the frequency of side-effect events between the intervention group and the control group is less than 10%

The prevalence of carbohydrate malabsorption that will be determined by hydrogen breath test will not be used to define acceptability.

#### 2.5.1.2 Efficacy trial

As stated in the hypotheses the main study will be a 3 group statistician blinded, randomized and controlled, parallel groups, **efficacy** non-inferiority trial. Because the participants will be able to distinguish the different RUTFs based on colour and mouth feel, participants will not be blinded. We will use the day care approach to ensure that children eat only the RUTF of the group to which they have been assigned. No study food will be taken home and the intake will be supervised by study enumerators who will in person feed the children.

The principal endpoints for the efficacy trial are:

1. Recovery rate
2. Mean weight gain
3. Mean time to recovery
4. Mean height gain
5. Percentage of body fat mass at recovery

6. Mean phase angle
7. Prevalence of anaemia
8. Incidence of deaths after discharge

The definition of principal endpoints is given below

(a) Recovery rate

The recovery rate will be measured as a percentage of those children who are discharged cured from the OTP programme divided by the total number of children who exit from the programme

$$\text{Recovery rate} = \frac{\text{No. children discharged Cured}}{\text{Total No. of Exit}} \times 100$$

(b) Average weight gain

The average weight gain will be measured as the mean of the growth velocity expressed in g/kg/day of individual children calculated as follow:

$$\text{Weight gain} = \frac{\text{Discharge weight (g)} - \text{Admission weight (g)}}{\text{Admission weight (kg)} \times \text{Length of stay (days)}}$$

$$\text{Average weight gain} = \frac{\Sigma \text{ weight gains}}{\text{Total children}}$$

(c) Average time to recovery or Length of stay

The average length of stay (LOS) is the mean of the LOS expressed in days of individual children calculated as follow:

$$\text{Average LOS} = \frac{\Sigma (\text{Discharge date} - \text{Admission date})}{\text{Total of children}}$$

(d) Average height gain

The average height gain is the mean of the height gain expressed in centimetres of individual children calculated as follow:

$$\text{Average height gain} = \frac{\Sigma (\text{Height 3 months after discharge (cm)} - \text{Admission height (cm)})}{\text{Total of children}}$$

(e) Prevalence of anaemia

The prevalence of anaemia will be expressed in percentage and calculated as follow

$$\% \text{ anaemia} = \frac{\text{n haemoglobin} < \frac{11.0\text{g}}{\text{dl}} * 100}{\text{total children with results}}$$

(f) Incidence of death after discharge

This endpoint will be expressed in person-months and calculated as follow:

$$\text{incidence of deaths} = \frac{\text{n deaths}}{\Sigma \text{ time of observation}}$$

(g) Percentage body fat mass

Percentage of body fat will be calculated by the laboratory performing the analysis. After determining total body water and total lean mass, the total body fat mass will be obtained by subtracting the lean mass to the total body weight. Then percentage body fat will be calculated as follow:

$$\%Body\ Fat\ mass = \frac{\text{Calculated Body Fat Mass(kg)} * 100}{\text{Body weight(kg)}}$$

(h) Phase angle

The phase angle will be provided by the BIA device.

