### **1.5.2.2 Efficacy trial**

Children staying within 1 hour walking distance from feeding points especially established in the community for the study will be enrolled and will be followed up from admission to nutrition recovery using a day care approach. Enrolled children will attend the site daily from 9 am to 3 pm. Children will be offered 200kcal/kg/day of one of the study RUTF. Children will be declared non-recovered if they don't meet the discharge criteria ( $MUAC \geq 12.5$  cm and no oedema) after 3 consecutive months of treatment. Apart from the difference in study therapeutic food, children of all the three study groups will be treated in the same way in accordance with the national guidelines for the treatment of SAM but using the day-care approach as stated above. The day-care approach allows the elimination of several confounding factors such as sharing or poor intake of the therapeutic food at households' level, inappropriate intake of routine medicines and differences in the product acceptance by caregivers that may affect child feeding of the study food. This approach will also allow close monitoring of side effects such as abdominal pain due to iron intake, flatulence (due to unabsorbed sugar), diarrhoea due to lactose intolerance and appetite suppression due to some oligosaccharides. Anthropometric parameters will be measured daily (weight and MUAC) or weekly (height). Clinical conditions will be assessed daily (appetite, oedema, cough, difficulty of breathing, diarrhoea, dehydration, fever, skin eruption, neurological status, anaemia). Embedded sub-studies will allow the assessment of

- haemoglobin (admission and discharge) with an Haemocue device that uses capillary blood collected at finger prick;
- body composition using deuterium dilution technique (at discharge for both those who recovered and those who did not recover);
- body composition using bio-electrical impedance analysis (at admission or when oedema subside, at time of reaching discharge criteria, at discharge and at 3 months follow up) using a Bodystat 1500 MDD device;
- breast milk intake using the dose-to-mother deuterium oxide dilution technique in children still breastfed at admission (two weeks after the start of the treatment);
- stool calprotectin using a quantitative point-of-care chromatographic immunoassay kit for the assessment of intestinal inflammation (admission, 28 days after the start of treatment, at discharge)

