Some experts believe that height gain is the best anthropometric indicator of increase in lean mass during nutrition rehabilitation and that weight gain without linear catch up may just indicate an increase in body fat[53]. However, the duration of nutrition rehabilitation for SAM is too short to demonstrate height catch up as many studies have demonstrated that weight gain precedes height gain by 3 to 4 months [49, 52, 54-56]. In addition it seems that height increment does not begin until children recovering from SAM have achieved at least 85% of expected weight-for-length meaning that they are usually discharged from therapeutic feeding program before height increment is seen [52]. Indeed, studies that have reported height gain during nutrition rehabilitation reported a modest height gain rate of around 0.2 mm/day [12]. Thus, height gain should be rechecked 3 to 6 months after recovery to identify any impact of treatment of SAM on catch up of linear growth. A study that distributed P-RUTF to prevent acute malnutrition during a hunger season in Niger has suggested that such catch up may occur [57].

A study in Uganda has revealed that fatty acid metabolism is important in the development of and recovery from SAM[58]. The findings of the study suggest that fatty acid metabolism regulate the adaptation to SAM with low levels of the adipose tissue hormone leptin being a strong predictor of the severity of and death from SAM[59]. The study also showed that plasmatic levels of many amino acids is reduced at the start of treatment suggesting contribution of protein metabolism to the phenomenon[58]. The serum level of the AA tested increased to maximum level within two weeks[58]. During that period, children were on the milk diet. There is no published similar data with RUTF especially for milk free RUTF. The lack of that information complicates optimisation of free milk RUTFs.

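### Height gain is not adjusted for length of stay, so a slower-recovering arm is credited with extra growing time; the weight-gain formula also masks part of a slower arm's deficit in children admitted with oedema

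*Protocol*

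**What the plan says.** Protocol section 2.5.1.2 lists weight gain and height gain among the principal endpoints and fixes a formula for each.

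- **Height gain, item (d):** "The average height gain is the mean of the height gain expressed in centimetres of individual children calculated as follow". The formula averages height 3 months after discharge minus height at admission. Nothing is divided by time, and the end visit is anchored to discharge, not admission.
- **Weight gain, item (b):** "The average weight gain will be measured as the mean of the growth velocity expressed in g/kg/day of individual children calculated as follow". The numerator runs from admission weight to "Discharge weight (g)". The denominator is "Admission weight (kg)" times "Length of stay (days)". The same formula applies whether or not the child was admitted with oedema.

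Both carry non-inferiority claims among the principal secondary hypotheses of section 2.3.2.2: 1.5 g/kg/day for weight and 0.5 cm for height in both age groups. The same list allows 14 days for time to recovery. Table 2 (section 2.5.3.1) uses 0.5 cm for height at 6-23 months but 0.3 cm at 24-59 months.

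Children with bilateral oedema are eligible (section 2.5.2.2), and Table 3 requires oedema to have been absent for 14 days at discharge. Section 2.4 says that "up to 80% of cases are oedematous in Malawi". For bioelectrical impedance, section 1.5.2.2 times the baseline "at admission or when oedema subside". Weight gain has no matching provision.

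**The concern.** Stay differs between children. Section 2.12 expects about 2 months to cure and 3 months for non-responders. It is also an outcome that the foods may change: section 2.1 reports more non-response to an earlier milk-free product in children under 24 months. A raw height difference over stay plus 3 months therefore mixes growth rate with observation time. If the test arm stays longer, the extra time offsets a real growth deficit, which is the unsafe direction in a non-inferiority comparison. If the control arm stays longer, the error runs the other way.

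The weight formula does divide by stay, so it lacks that fault. Its weakness is the starting point. A child admitted with oedema loses fluid before leaving, and the formula subtracts that fluid from tissue gained. The fluid term is spread over the stay, so it costs a slower arm less per day than a faster one, and the gap between them shrinks.

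**Working it through.** **Height: inputs.** The 14-day difference is the time-to-recovery margin (section 2.3.2.2). For growth rate, section 2.1 says that studies "reported a modest height gain rate of around 0.2 mm/day" during rehabilitation; the range 0.1 to 0.3 mm/day is my assumption. Table 2 gives, with 10% loss, SD 0.7 cm, margin 0.5 cm and 180 per arm at 6-23 months, and SD 0.8 cm, margin 0.3 cm and 100 per arm at 24-59 months.

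*The plan's own figure.* For 24-59 months, n = 2 x (1.645 + 0.842)^2 x 0.8^2 / 0.3^2 = 88, and 88 / 0.9 = 98 against the stated 100. A one-sided 5% test with 80% power therefore reproduces it. For 6-23 months the same formula gives 25, or 28 after loss, not 180. That is a separate matter and is not evidence for this point.

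*Size of the bias.* Bias = growth rate x difference in stay.

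| Rate (mm/day) | 14 extra days (cm) | Share of 0.5 cm | Share of 0.3 cm |
|---|---|---|---|
| 0.1 | 0.14 | 28% | 47% |
| 0.2 | 0.28 | 56% | 93% |
| 0.3 | 0.42 | 84% | 140% |

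At 0.2 mm/day, 7 extra days add 0.14 cm. Equal stays add nothing.

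*Illustration.* Let two arms both grow at 0.02 cm/day, with stays of 60 and 74 days plus 90 days of follow-up. Raw gains are 150 x 0.02 = 3.00 cm and 164 x 0.02 = 3.28 cm. Per 30 days, both are 0.60 cm.

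*Effect on the claim.* Suppose the true equal-time deficit equals the margin and the test arm stays 14 days longer. The chance of declaring non-inferiority is Phi(0.28/SE - 1.645), with SE = SD x sqrt(2/n) and n the evaluable number per arm after 10% loss.

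- 24-59 months: n = 90, SE = 0.119 cm, chance about 76% instead of 5%.
- 6-23 months: n = 162, SE = 0.078 cm, chance about 97% instead of 5%. With only 25 evaluable per arm it would be about 41%.

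Under the two-sided 95% interval of section 2.5.6.2.1 the chances are about 65% and 95% (n = 90 and 162), against a nominal 2.5%.

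**Weight: inputs.** The protocol gives no fluid fraction, dry weight or tissue gain. I assume dry weight D = 7 kg, tissue gain T = 1.0 kg in both arms, and stays L of 40 and 54 days. Fluid F is 3%, 5% or 10% of D, and admission weight is W0 = D + F.

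Protocol formula: 1000 x (T - F) / (W0 x L). Oedema-free version: 1000 x T / (D x L).

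- Oedema-free: 3.57 v 2.65, a deficit of 0.93 g/kg/day for the slower arm.
- Protocol formula at 3% fluid: 2.74 v 2.03, deficit 0.71.
- At 5% fluid: 2.21 v 1.64, deficit 0.57.
- At 10% fluid: 0.97 v 0.72, deficit 0.25.

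Before rounding, the hidden part is 0.216, 0.353 or 0.673 g/kg/day in oedematous children. If 80% of an arm were oedematous, the arm mean would hide 0.8 times that: 0.17, 0.28 or 0.54, which is 12%, 19% or 36% of the 1.5 margin.

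**The case against.** The height bias is conditional. It needs a difference in mean stay, and 14 days is the edge of what the protocol tolerates. Time to recovery is its own principal secondary endpoint, so a delay that large would be visible. This stands, but seeing a delay does not correct the height comparison, and a delay inside 14 days would pass both tests.

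On weight, a reader might infer that the formula favours the slower arm. The documents do not support that: the formula divides by stay, so in the cases above the slower arm still scores lower. At equal total tissue gain the order reverses only when fluid lost exceeds tissue gained. With equal daily tissue gain the slower arm does score 0.19, 0.31 or 0.59 g/kg/day higher at 3%, 5% or 10% fluid, but that arm has then also gained more tissue in total.

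A reader might also set the level error beside the margin. With 5% of a 7.0 kg admission weight as fluid, true gain of 5 g/kg/day and 40 days' stay, the formula gives 3.5, an error of 1.5, the same number as the margin. The two are not comparable. That error falls on oedematous children in every arm, and randomisation within age group balances admission oedema in expectation. The margin concerns the difference between arms.

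The 80% is an upper figure for Malawi, not a forecast of the trial's case mix. The planned oedema subgroups (section 1.5.4.2) and interaction checks (section 2.5.6.2.1) help interpretation, but they reuse the same formulas and cure neither defect.

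**Conclusion.** The height point holds. As defined, the endpoint credits a slower arm with growing time. At the protocol's own growth rate, a 14-day longer stay is worth 0.28 cm (0.14 to 0.42 cm over the assumed range of rates), more than half of the 0.5 cm margin and nearly all of the 0.3 cm. This assumes that the cited rate applies to the added days, and it vanishes when mean stays are equal.

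The weight point holds only in a narrower form. Starting from oedematous weight dilutes a slower arm's deficit in children admitted with oedema, by an amount that depends on assumed inputs. There is no such bias in non-oedematous children.

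Both are secondary endpoints. The recovery-rate primary does not use either formula.

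**What to change.** **Height.** Replace the raw difference with each child's height gain divided by the actual time from admission to the 3-month visit, in cm per month. Alternatively, scale it to a common interval of about 5 months (2 of treatment plus 3) so that a centimetre margin can be kept. State the margin on the chosen scale: over 5 months, 0.5 cm is 0.10 cm per month and 0.3 cm is 0.06. This is only a conversion. Section 2.3.3 bases these margins on an earlier trial's confidence intervals, so margin and SD should be re-expressed from those data, and the 0.5 and 0.3 cm for older children reconciled at the same time. No new measurements are needed. Dividing by time assumes roughly steady growth over the interval, which the report should say.

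**Weight.** Keep the admission-weight formula. Beside it, add an analysis of children admitted with oedema that starts from their oedema-free (minimum) weight, taken from the daily weight and oedema records. It should be an addition, not a replacement: that baseline arises after randomisation and may depend on the food, restarting the clock there drops the time taken to clear oedema, and children who exit before oedema clears have no such weight. Report their number by arm. The cost is one extra analysis from data already collected.
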